### Criteria for discontinuing or modifying allocated interventions {11b}

In this study, the criteria for discontinuing the intervention will be (1) participants who fail to attend two or more sessions, and (2) participants who request to withdraw from the trial.

### Strategies to improve adherence to interventions {11c}

The therapists of intervention groups will encourage the participants to attend intervention sessions. If a participant is absent from a session, a research member will contact personally.

### Relevant concomitant care permitted or prohibited during the trial {11d}

In this trial, participants who receive another intervention during their participation in the study will be excluded.

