### Trial design {8}

This is the protocol of a parallel-group, controlled, randomized trial, with a pre-post and repeated follow-up measures between-group design.

A three-arm trial is going to be carried out. Participants who meet the recruitment criteria bellow will be randomly assigned to Group 1: Water exercise group, Group 2: Land exercise group, or Group 3: Control group. The assessment will be conducted at five-time points: an initial assessment before being randomized (pretreatment; T0), at the end of the intervention (post-treatment; T1), 3 months after the completion of the intervention (T2), 12 months after the completion of the intervention (T3), and 24 months after the completion of the intervention (T4). CONSORT patient’s flowchart is presented in Fig. 1.

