### Intervention description {11a}

(A) Water exercise group where the Ai-Chi technique was selected as the exercise method of choice. The activity will take place in a hydrotherapy pool approved by the Ministry of Health and will be led by a hydrotherapist who has been trained in Ai-Chi.(B) Land exercise group who will perform the same Ai-Chi movements on land in order to standardize the groups. The activity will take place in a hall and will be led by a physiotherapist who has been trained to teach Ai-Chi on land.(C) Control group who will not perform additional physical activity or receive any extra treatments. In accordance with the recommendations for physical activity among cancer patients and the guidance of the hydrotherapy organization for hot water activities, the exercise program will be scheduled for 30 min twice a week for 8 weeks. The physical activities will take place in groups of 5 participants per group.

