### Outcomes {12}

Data will be collected by a medical student in the fourth year of studies at the following time points: before the start of the intervention (at baseline), after 8 weeks of intervention, and then at 3, 12, and 24 months from the end of the intervention.

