### Sample size {14}

One hundred and fifty cancer patients aged 18–65 years (stage III colon cancer patients and breast cancer patients with lymph node involvement) will be recruited via advertisements in Hadassah Medical Center and Tal Aviv University. The sample size is based on data from the WHO Disability Assessment Schedule (WHODAS 2.0), which has been used internationally to assess function and disability among a healthy population versus an unhealthy population [26]. The expected difference in the questionnaire scores between the two groups is 15 points and the average standard deviation is 15.08. The sample calculation includes a type 1 error of alpha equal to 0.05 with a power of 80%. According to this calculation, 16 participants are needed in each of the three study groups. Because we anticipate the withdrawal of some of the participants and because of the clinical condition of all participants, a number of 50 participants per group was selected.

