### Assignment of interventions: Blinding

#### Who will be blinded {17a}

Due to the nature of this intervention, treatment allocation cannot be blinded to the participants or to the caregivers. Participants receive an explanation about the type of intervention, and caregivers are aware that everyone is a patient and know what type of treatment they provide.

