### Methods in analysis to handle protocol non-adherence and any statistical methods to handle missing data {20c}

To address protocol non-adherence, intervention physiotherapists will receive intervention protocol. Missing data will be imputed using the random forest method.

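### The concomitant-care rule excludes participants who receive another intervention, most naturally through 24-month follow-up, and nothing keeps them in follow-up or analysis; this biases the comparison if removal relates to outcome and differs by arm

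*Protocol article*

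**What the plan says.** The rule is one sentence in the protocol article, section {11d}: "participants who receive another intervention during their participation in the study will be excluded". It does not define another intervention, gives no time window, and does not say what the person is excluded from.

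Four other sections bear on how it works:

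- **Trial design {8} and Outcomes {12}.** The first assessment precedes randomisation. Later data are collected "after 8 weeks of intervention, and then at 3, 12, and 24 months from the end of the intervention".
- **Intervention description {11a}.** The third arm is a "Control group who will not perform additional physical activity or receive any extra treatments". No end date is given for that restriction.
- **Criteria for discontinuing {11b}.** Stopping the allocated programme is handled separately, by missed sessions or a request to withdraw.
- **Non-adherence and missing data {20c}.** On non-adherence the only provision is this: "To address protocol non-adherence, intervention physiotherapists will receive intervention protocol". A second sentence says that missing data will be imputed by random forest. It does not say whether that extends to people excluded under {11d}.

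The trial is open: "treatment allocation cannot be blinded to the participants or to the caregivers".

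**The concern.** Randomisation makes the arms comparable as they were formed. That protection lasts only while everyone randomised is followed and compared in the assigned arm. A rule that drops people for something they do after randomisation makes the result depend on who those people are and how many come from each arm.

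Different rates are plausible here. Allocation is known, follow-up is long, and only the controls are described as having no added activity or treatment. Controls might take up other exercise or rehabilitation more often, and doing so could go with better or worse function. If the controls removed are those doing better, a benefit of exercise is overstated. If they are those doing worse, it is understated. The article contains nothing that would show which of these happens, or whether either does.

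**Working it through.** **1. The plan's own figure.** Sample size {14} uses WHODAS 2.0 with a difference of 15, SD 15.08, alpha 0.05 (two-sided assumed) and 80% power. n = 2 × (1.960 + 0.842)² × (15.08/15)² = 15.9, so 16 per group, as stated. The t-test version gives 16.9, so 17. The point does not depend on this figure, but the SD and the chosen 50 per arm are used below.

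**2. Whom the rule reaches.** Randomisation follows the baseline assessment, and taking part includes visits to 24 months after the programme. Read together, the {11d} rule covers randomised people over the 8 weeks and the two years after. Because {11b} uses discontinuing for leaving the programme, the different word in {11d} is best read as removal from the study. Both steps are inferences from the wording.

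**3. Size of the bias at one time point.** Assumptions, none of them from the article: a share p of each arm would receive another intervention; these people differ in outcome by d = 0.5 × 15.08 = 7.54 points; there is no true effect; 50 per arm. All such controls are removed, and a fraction f of such exercisers.

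The share of these people left in an exercise arm is q = p(1 − f)/(1 − pf). None are left among controls, so bias = q × d.

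- p = 0.2, f = 0: q = 0.20, bias = 0.20 × 7.54 = 1.5 points.
- p = 0.2, f = 0.5: q = 0.10/0.90 = 0.111, bias = 0.8 points.
- p = 0.2, f = 1: q = 0, bias = 0.

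Simulation (100,000 runs per case, two-sample t-test at 5%) agrees:

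| Uptake p | Exercisers removed | Bias (points) | False-positive rate |
|---|---|---|---|
| 20% | none | 1.51 | 7.5% |
| 20% | half | 0.83 | 5.8% |
| 20% | all | −0.01 | 4.9% |
| 10% | none | 0.76 | 5.6% |
| 40% | none | 3.02 | 13.7% |
| any, everyone kept | – | 0 | 4.9% to 5.1% |

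If those removed do worse instead of better, the sign reverses and the rates are essentially unchanged.

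**4. A different removal mechanism.** Remove people on a variable correlated with outcome. With correlation 0, even 40% against 10% removed gives about 0 bias and 5%. With equal removal of 10%, the bias is about 0 at correlations of 0.3 and 0.5. With 20% against 10%, it is 0.7 to 1.2 points and 5.5% to 6.6% over correlations 0.3 to 0.5. Both conditions are therefore needed: removal related to outcome, and removal unequal between arms.

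**5. Change from baseline.** Statistical methods {20a} plans mixed variance analyses by group and over time, so step 3 was repeated on change from baseline (p = 0.2, controls only removed, assumed baseline correlation 0.6). If the 0.5 SD difference is already present at baseline, it cancels: about 0 points and 5.0%. If it arises later, the result is 1.5 points and about 8%.

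**6. Cost of keeping everyone.** Suppose a share u of controls takes up fully effective exercise. The expected difference is 15(1 − u), and the control SD is √(15.08² + u(1 − u) × 15²).

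- u = 0.2: difference 12, control SD 16.23. Power is 97% at 50 per arm and 88% at an assumed 35.
- u = 0.4: difference 9, control SD 16.78. Power is 80% at 50 per arm and 64% at 35.

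The 35-per-arm case is shown because the sample-size section says "we anticipate the withdrawal of some of the participants" without giving a rate.

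**The case against.** The strongest reply has four parts.

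- **The wording is open.** The rule has no window and sits next to items about attending sessions, so it may be meant for the 8 weeks only. Excluded may mean from further treatment, not from analysis. Analysis populations are usually left to an analysis plan, and imputation might bring these people back in. This stands in part: the 24-month reach and removal from analysis are the natural reading, not stated facts. A reader might also infer that {20c} is silent on missing data; it is not, but it does not link imputation to excluded people. The reply does not dispose of the point, because the article makes a positive commitment to exclude. An analysis plan that kept these people would have to depart from it, and visits never made cannot be recovered afterwards.
- **The planned analysis is not a single-time comparison.** This stands. A difference already present at baseline cancels in a change analysis, so the illustration needs a difference that arises later.
- **The rule covers all three arms.** This also stands. Control-only removal is an upper case for a given uptake, not what the rule prescribes. A reader might infer from the control-arm description that the rule falls only on controls. That text describes what the arm receives and does not alter how the rule applies.
- **Keeping everyone also moves the estimate.** On the inputs in step 6, it shrinks by 3 points at 20% uptake and 6 at 40%. That is a change in the question answered (the effect of assignment with other care allowed), not a bias, but it is a real cost.

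**Conclusion.** The point holds in conditional form. As written, the rule excludes participants for an event that most naturally falls after randomisation, and nothing in the article keeps them in follow-up or analysis. Validity then rests on removal being unrelated to outcome or equal between arms, and the article supports neither assumption.

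Under the assumptions shown, the distortion runs from about 0 points and 5% (equal removal), through 0.8 points and about 6% (half as many exercisers removed), to 1.5 points and about 7.5% to 8% as an upper case at 20% uptake. Uptake, the 0.5 SD difference and its timing are all assumed.

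A reader might infer that the rule will exaggerate the benefit of exercise. The article does not support that: it gives no removal rates and no link to outcome, so the bias could go either way or be absent. The change is still worth making while recruitment and follow-up continue, because it removes the dependence at little cost.

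**What to change.** In section {11d}, replace *will be excluded* with: *receipt of another intervention is recorded in the same way in all three arms; the participant stays in the assigned arm, completes all assessments to T4 and is analysed as randomised*. Label any analysis that omits these participants as supplementary.

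The cost is a one-sentence amendment, with the ethics approvals that the protocol requires for any change, and a record of other interventions at the existing visits. No extra visits or participants are needed. The downside is dilution if controls take up effective exercise. With 50 per arm, the planned 80% power is roughly kept even at 40% fully effective uptake. With heavy withdrawal as well, it would not be.

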### Provisions for post-trial care {30}

No potential harm is expected from this study.

### Outcomes {12}

Data will be collected by a medical student in the fourth year of studies at the following time points: before the start of the intervention (at baseline), after 8 weeks of intervention, and then at 3, 12, and 24 months from the end of the intervention.

### Primary outcome

Employment Barriers Questionnaire [25] and Date of return to work and duration of working hours—self-report by the study participants.WHODAS 2.0—to examine the degree of activity and participation in daily life [26].EORTC QLQ-C30—to evaluate the quality of life from the point of view of the participant [27].

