### Objectives {7}

Based on the literature review described above, the objectives of the present study are:

(A) To examine the effects of an 8-week physical activity program in water, on time to return to work, work hours, perception of work-related difficulties, and work absenteeism, among cancer patients, as compared to an intervention group undergoing identical physical exercise on land, and a third group with no additional exercise.(B) To examine the effects of an 8-week physical activity program in water on activity and participation in the daily life and quality of life of cancer patients compared with the other two intervention groups (the same physical activity on land and the group without further physical exercise).(C) To examine the effects of an eight-week water exercise program on exhaustion, fatigue, and neuropathy in cancer patients compared with the other two intervention groups (the same physical exercise on land and the group without further physical exercise).

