### Eligibility criteria {10}

Criteria for inclusion in the study will be: (a) age between 18–65; (b) diagnosis of cancer; and (c) a score above 26 on the cognitive MOCA test [24]. Volunteers with orthopedic injuries that in the opinion of the attending physician prevent their participation in physical exercise, or individuals engaged in other physical activity on a regular basis, will not be eligible to participate in the present study. Recruitment of colorectal cancer patients and breast cancer patients for the study will be within 3 months of cessation of chemotherapy treatment.

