### Statistical methods

#### Statistical methods for primary and secondary outcomes {20a}

Every participant will be assigned a random study identifier number, ensuring the privacy of their personal data. The statistical analyses will be conducted in a way that prevents the identification of individual patients. We will conduct a series of mixed variance analyses to identify relationships and associations between groups, as well as changes over time within each group (independent variables). The dependent variables will be primary and secondary outcomes, and a separate analysis will be performed for each variable.

Additionally, we will conduct various analyses to explore the relationships between changes in the dependent variables.

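### For participants not working at T0, baseline working hours are zero and cannot absorb differences in usual job hours; asking for pre-diagnosis hours would regain precision

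*Protocol article*

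**What the plan says.** The Primary outcome section of the protocol article names "Date of return to work and duration of working hours", as reported by participants themselves, next to the Employment Barriers Questionnaire, WHODAS 2.0 and QLQ-C30. Objective A under Objectives {7} covers "time to return to work, work hours, perception of work-related difficulties, and work absenteeism". Outcomes {12} sets data collection "before the start of the intervention (at baseline), after 8 weeks of intervention, and then at 3, 12, and 24 months from the end of" treatment.

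Statistical methods {20a} plans mixed variance analyses, with group and time as the independent variables, and adds: "The dependent variables will be primary and secondary outcomes, and a separate analysis will be performed for each variable". It names no covariate.

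Eligibility {10} requires "a) age between 18–65; (b) diagnosis of cancer; and (c) a score above 26 on the cognitive MOCA test", excludes certain orthopedic injuries and regular exercisers, and times recruitment "within 3 months of cessation of chemotherapy treatment". It sets no condition on employment, either before diagnosis or at entry. No pre-diagnosis working hours are mentioned, and the period that the baseline hours question covers is not stated.

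**The concern.** In a group-by-time analysis the T0 value normally carries stable differences between people, so that they do not inflate the error of the comparison over time. WHODAS, QLQ-C30, Piper and CIPN20 scores at T0 can do this.

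Current working hours cannot do it for someone not working at T0. That value is zero whether the usual job was 20 hours, 40 hours or none. Change from T0 then equals the follow-up value, and as a covariate T0 is constant across these people. A part-timer fully back at her usual hours counts as half of a full-timer who is equally recovered, and that difference stays in the error term. What is at stake is precision, and so power, for one of the work outcomes that the trial puts first.

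**Working it through.** **The plan's own figure.** Sample size {14} uses a WHODAS difference of 15, SD 15.08, alpha 0.05 and power 80%. The normal formula, two-sided, gives n = 2 × (1.960 + 0.842)² × (15.08/15)² = 15.87, so 16 per group, as stated. This concerns WHODAS only. No difference, SD or power is given for working hours, so every input below is an assumption, apart from the 50 per arm and alpha 0.05 (taken as two-sided).

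**Share of variance explained.** Let c be usual weekly hours before diagnosis and p the probability of being back at work. Suppose that those back work c hours and the others zero. Then

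share = p² Var(c) / (p E[c²] − p² E[c]²).

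- *Main scenario:* c = 20 (40%) or 40 (60%). E[c] = 32, E[c²] = 1120, Var(c) = 96. At p = 0.6: 34.56/303.36 = 11%. At p = 0.8: 61.44/240.64 = 26%.
- *Some not employed before illness:* c = 0 (20%), 20 (30%) or 40 (50%). E[c] = 26, E[c²] = 920, Var(c) = 244. At p = 0.6: 87.84/308.64 = 28%. At p = 0.8: 156.16/303.36 = 51%.
- *Similar hours for all:* c = 30 (30%) or 40 (70%). E[c] = 37, E[c²] = 1390, Var(c) = 21. At p = 0.5: 5.25/352.75 = 1.5%. At p = 0.9: 17.01/142.11 = 12%.

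**Check with a graded return.** A second simulation took pre-diagnosis hours with mean 36 and SD 10, and returners working about 80% of their former hours. The share explained was 3%, 6%, 12%, 28% and 54% with 30%, 50%, 70%, 90% and 100% back. The gain is small early and material only once most have returned.

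**Power.** Take one two-arm comparison at one time point, 50 per arm, with 80% versus 55% back, in the main scenario.

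- Difference: (0.80 − 0.55) × 32 = 8.0 hours.
- Variances: 240.64 at p = 0.80; 0.55 × 1120 − 0.55² × 32² = 306.24 at p = 0.55.
- Unadjusted SE: √((240.64 + 306.24)/50) = 3.31 hours.
- In 6,000 simulated comparisons, adjusting for c lowered the mean SE from 3.31 to 3.04 hours and raised power from about 66% to 73%.
- With 20% not employed before illness, the SE fell from 3.48 to 2.78 hours and power rose from about 45% to 63%.
- With 30 or 40 hours for all, power rose only from about 75% to 76%.
- The type I error stayed near 5% with and without adjustment.

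**Where the covariate must enter.** A main effect that is constant over time shifts all of a person's visits equally and cancels from any change between visits. Usual hours have no bearing on a T0 value of zero but do affect later hours, so the group-by-time test gains only if the covariate's effect may differ by visit.

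**The case against.** The strongest objection is that the premise covers only some participants. Eligibility {10} does not require anyone to be off work. People within 3 months of chemotherapy may already work full or reduced hours, and the absenteeism aim fits people in work. Their T0 hours do carry information: in the graded-return simulation with 10% to 50% already on reduced hours at T0, T0 hours correlated with later hours at 0.03 to 0.72, depending on the return rate. This stands. A reader might infer that working hours have no informative baseline at all, but the article does not support that.

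A reader might also infer that a chance imbalance in part-time and full-time jobs would pass for an exercise effect. That does not follow either. Under randomisation such imbalance is random error, already covered by alpha, and the simulated error rate stayed near 5%.

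A further objection is that a condensed article may leave covariates and baseline items to the full protocol or SAP, and that the schedule figure and the questionnaire's content cannot be seen. This is fair, and the point should not be read as a charge of omission. It compares the stated model with a better one that costs little. It also concerns data collection: an SAP cannot adjust for an answer that nobody was asked for.

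Last, the size is assumed throughout. The power figures are for a single two-arm comparison without dropout, whereas the trial has three arms, repeated measures and expected withdrawals. This also stands, so the result is given as a range.

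**Conclusion.** The point holds as a matter of precision, for participants not working at T0. Their baseline hours are zero, and the stated group and time factors leave differences in usual job hours in the error term. The comparison remains valid and no stated figure in the article changes.

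The loss runs from about 2% of follow-up variance, when hours are alike and few are back, to about 50%, when contracts are mixed, some had no job and most are back. The main scenario gains about 7 percentage points of power (66% to 73%). These figures depend on the assumed mix of hours and return rates. They do not show that the trial is underpowered for working hours, because the article gives nothing against which to judge that. The change is worth making because it is cheap and recruitment is expected to run to August 2027.

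**What to change.** - Add one question at T0: usual paid weekly hours before diagnosis, recorded as 0 if none. If this is already collected, only the analysis text needs changing.
- Pre-specify the answer as a covariate, with a covariate-by-time term, in the working-hours model, and as a covariate in the return-to-work analysis.
- Report hours as a share of pre-diagnosis hours only as a supporting result, restricted to participants with non-zero pre-diagnosis hours, since the share is undefined for the others.
- Ask those already enrolled at their next contact. The fact asked about predates randomisation, but the recall would follow allocation in a trial where participants know their group. Run a sensitivity analysis without the late-collected values.

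The cost is one extra question, a few lines of analysis text and that sensitivity analysis. The remaining downside is recall error in the late answers.
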